## Result Evaluation:

A total score higher than 41 on the Children's Sleep Habits Questionnaire (CSHQ) indicates poor sleep

00 quality.

### A5.1 Roles and responsibilities:

The Principal Investigator will ensure adherence with the protocol, regulatory standards and ethical guidelines, as well as accuracy in relation to data entry. The P.I will also monitor safety adverse events reported during the study, according to safety monitoring plan specific in the trial protocol section 7. The P.I will perform data and safety monitoring through making regular contact with the relevant personnel in charge of on-site monitoring at each of the participating sites, through phone calls and WeChat messaging and email. In addition, the P.I will make no less than one trip every 4-6 months, in person, to each of the participating sites within the study period, to ensure that study data is authentic, complete and the data entry accurately correlates with the hardcopy data forms.

The Principal Investigator will provide an update of findings to DSMC via a monthly report, disseminated to all members of the DSMC via email and/or WeChat for decision. The monthly report will include data integrity reports and summary SAEs reports from each site that identify any emerging trends or safety concerns. Emergency meetings may be called if it is in relation to safety adverse events. Thorough records of all monitoring activities, findings, and actions taken will be kept.

## **A5.2 Interim analysis:**

Interim analyses will be performed when data collection has been completed for 50% ( 170 out of the 340) targeted subjects, with 85 in each group.

## **A5.3 Statistical interim analyses:**

Primary outcome measure: Autism Treatment Evaluation Checklist (ATEC) total and subdomain scores will be used for analysis of change in social functioning. T-tests, ANOVA and ANCOVA will be used to examine the rate of improvement for these scores. Scores will be compared with baseline. Estimates of the difference in the average rate of improvement in the scores will be obtained. These estimates will then be tested against the null value of no difference between both groups.

Secondary Outcome measures: Autism Behaviour Checklist (ABC) total and subdomain scores will be used for analysis of change in social functioning. The Childhood Sleep Habits Questionnaire (CSHQ) will be used for analysis of change in sleep functions. Scores will be compared with baseline. Estimates of the difference in the average rate of improvement in the scores will be obtained. These estimates will then be tested against the null value of no difference between both groups.

Participant characteristics at baseline (including demographic and clinical) will be compared within each group using independent sample t-tests or chi-square test as appropriate for the variable.

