### 9.2 Statistical and Analytical Plans

#### 9.2.1 General Considerations

Statistical analysis will be implemented using the IBM SPSS version 27.0. Before applying any statistical test, the data sets will be tested for a normal distribution with the Shapiro–Wilk test. If the data was found to be normally distributed, then one- way analysis of variance ANOVA and Student’s t-test will be used for the comparison between groups. Analysis of Covariance ANCOVA will be used to compare one or more means between groups

while controlling for the effects of one or more covariates (continuous variables that are related to the dependent variable). For comparison with the baseline value, paired t-test or one-way analysis of variance (ANOVA) will be used to compare the differences within the group before and after treatment. If the data was found to be not normally distributed then Kruskal-Wallis test or Mann-Whitney rank-sum test was used for the comparison. In order to correct for multiple comparisons, Bonferroni correction will be used to further validate the significance of each p-value. All statistical tests were conducted using a two-sided test. The  $\alpha$ -value was set to 0.05 for all the statistical tests and < 0.01 for Bonferroni correction. Chi-Squared test was used for categorical data, and Mann-Whitney rank sum test was used for ordinal data.

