## **A5.4 Interim Analyses Reporting:**

The P.I will be responsible to present interim findings to the DSMC, the trial sponsor and regulatory health authorities of Foshan Science and Technology Bureau, Guangdong Provincial Health Commission, China.

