## **A5.6 Trial Audit:**

Members of the DSMC committee will meet in person, or virtually over Tencent Web Conference , once in every 6 months, to discuss findings from the monthly reports and interim report submitted by the P.I. Decisions taken will be by majority vote of the committee, independent from the sponsor and investigators.

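### The half-way interim analysis tests efficacy between arms with no decision rule, boundary or alpha allocation, and the principal investigator presents the comparative result to the sponsor

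*Combined protocol and SAP*

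**What the plan says.** **Timing (A5.2).** "Interim analyses will be performed when data collection has been completed for 50" percent of the target, that is 170 of 340 children, 85 per group.

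**Content (A5.3).** The interim covers ATEC total and subdomain scores as primary, and ABC and CSHQ as secondary. For both sets, differences in average improvement are estimated, and "These estimates will then be tested against the null value of no difference between both groups".

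**Significance level (9.2.1).** "All statistical tests were conducted using a two-sided test", and alpha "was set to 0.05 for all the statistical tests and < 0.01 for Bonferroni correction". The purpose of the second level is given as: "In order to correct for multiple comparisons, Bonferroni correction will be used to further validate the significance of each p-value". Neither sentence mentions the interim look.

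**Reporting (A5.4).** "The P.I will be responsible to present interim findings to the DSMC, the trial sponsor and regulatory health authorities".

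**Decisions (A5.6).** The DSMC meets every six months to discuss the monthly reports and the interim report submitted by the principal investigator. "Decisions taken will be by majority vote of the committee, independent from the sponsor and investigators".

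**Blinding (6.4).** Children, their parents or caretakers, and the outcome evaluators are blinded. The principal investigator and the sponsor are not on that list.

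**The concern.** There are two separate gaps.

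The first is inferential. A significance test of the primary outcome goes to a committee that takes decisions, and nothing says how the p-value is to be used. If a small p-value at 170 children could end the trial or be reported as success, the null hypothesis gets two chances to be rejected, and the final test at 0.05 no longer gives an overall 5%.

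The second is about conduct, and holds whatever is decided on alpha. The person who presents the comparative result also visits every site at least once every 4 to 6 months and oversees data entry (A5.1), and has access to the full data (11.1). Several drop-out criteria in 3.7 need judgement, such as poor compliance or significant missing items. A principal investigator and sponsor who know the half-way effect could influence the second half without intending to.

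**Working it through.** **1. The plan's own figure.** The documents state no overall type I error across looks. The nearest stated figure is 120 per group (9.1), with d = 0.36 and 80% power. A two-sided 5% comparison of two independent means gives n = 2 × ((1.960 + 0.842)/0.36)² = 121.1 per group, close to the stated 120. A two-sided, between-arm test is therefore the right basis for what follows.

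**2. Inputs.**
- Interim: 170 children with complete data (A5.2).
- Final number with complete data: 340 (no dropout), 240 (2 × 120, from 9.1), or 340 × 0.6 = 204 (the 40% dropout assumed in 9.1).
- Information fraction t: 170/340 = 0.50, 170/240 = 0.71, 170/204 = 0.83.
- Level per look: 0.05 (|Z| > 1.960) or 0.01 (|Z| > 2.576), both from 9.2.1.
- Assumption, not in the plan: a significant interim result can stop the trial or be claimed as success.

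**3. Error over two looks.** Under the null, the two test statistics are bivariate normal with correlation √t. The overall error is P(|Z₁| > c or |Z₂| > c).

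| Final number | t | √t | 0.05 at both looks | 0.01 at both looks |
|---|---|---|---|---|
| 340 | 0.50 | 0.707 | 8.31% | 1.77% |
| 240 | 0.71 | 0.842 | 7.52% | 1.60% |
| 204 | 0.83 | 0.913 | 6.91% | 1.46% |

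These figures are for one endpoint. If the interim can neither stop the trial nor support a claim, only the final test counts and the error is the nominal 5% (or 1%).

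**4. Does the 0.01 level already cover the interim?** It would equal 0.05/5, which fits ATEC total plus four subscales, although the plan does not say so. On that reading it is fully used on the five scores, and the second look still raises the per-endpoint error from 1% to between 1.5% and 1.8%. The plan also does not say which level applies at the interim.

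**5. Boundaries that hold 5%.** The two-look O'Brien-Fleming boundary at t = 0.50 is |Z| > 2.797 (p < 0.0052), then |Z| > 1.977 (p < 0.0480), for an overall error of 5.00%. Left unchanged at t = 0.71 and 0.83, it gives 4.87% and 4.82%, so it is slightly conservative if dropout raises the information fraction.

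**6. Power cost.** With 120 per group and d = 0.36, the expected Z is 0.36 × √60 = 2.789. Power of the final test is Φ(2.789 − 1.960) = 79.6% at 0.05 and Φ(2.789 − 1.977) = 79.1% at 0.048, a loss of about 0.5 points.

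**7. Reporting and independence side by side.** A5.4 makes the principal investigator the presenter, and the sponsor a recipient, of the interim findings. A5.6 says that the committee's decisions are independent of both. The text reviewed describes no separate analyst, closed report or limit on who sees by-arm results.

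**The case against.** **The inflation is conditional.** A reader might infer that type I error simply rises to about 8%. The documents do not support that. No section says that efficacy can be declared or the trial stopped at the interim, and A5.6, headed as trial audit, describes committee decisions in general rather than an efficacy vote. This stands. But A5.6 does place the interim report before a committee that votes, so stopping is not excluded either. The defect is that the purpose and the rule are not stated.

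**0.05 is not the only level given.** Section 9.2.1 also gives 0.01. This stands, and the figures above show both. It does not close the gap, because that level is for multiple comparisons.

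**The trial is not shown to be unblinded.** A reader might infer that A5.4 unblinds the trial team and defeats the double-blind design. Section 6.4 limits blinding to families and outcome evaluators, 6.4.1 keeps assessors out of allocation and treatment, and nothing sends them the interim result or any individual allocation. The principal investigator and co-investigators also have data access throughout (11.1). All of this stands. What remains is that a formal by-arm efficacy comparison is put before the principal investigator and sponsor in mid-trial.

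**A5.4 does not contradict A5.6.** A5.6 claims independence of decisions, not sole access to results. The two sit uneasily together, but they are not logically inconsistent.

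**Part of the text was unavailable.** The text just before A5.1 was not available for this review, and the numbering runs from A5.4 to A5.6. Absence is claimed only for the text reviewed.

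**Conclusion.** The point holds in this form. The plan sets a between-arm efficacy test at 170 of 340 children without a decision rule, stopping boundary or alpha allocation, and gives the comparative aggregate result to the principal investigator and sponsor before the trial ends.

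If the interim can stop the trial or support a claim, the type I error for one endpoint is 6.9% to 8.3% at 0.05 per look, or 1.5% to 1.8% at 0.01 per look. The range reflects an information fraction from 0.83 down to 0.50, which depends on how many children complete. If the interim can do neither, the error is 5% and the statistical part is settled by saying so.

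The missing firewall does not depend on that choice. It is a risk to trial conduct, and its size cannot be computed from the documents. Both parts need to be settled before the interim data are analysed, because a rule written after the result is known would carry little weight.

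**What to change.** **A5.3, preferred.** State that there is no stopping for efficacy, and remove the between-arm efficacy tests from the interim. Report safety, accrual, data quality and pooled dropout only. The final alpha stays at 0.05, at no cost.

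**A5.3, alternative.** If an efficacy look is wanted, test ATEC total only, against an O'Brien-Fleming-type boundary set at the actual information fraction. At t = 0.50 this is interim p < 0.0052 and final p < 0.0480. State the final level in 9.2.1, and state there that the Bonferroni level does not cover repeated looks. The cost is about 0.5 points of power at 120 per group and d = 0.36.

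**A5.4.** If any by-arm results are produced, an analyst already on the study, with no role in recruitment, treatment or assessment, sends them to the DSMC only. The principal investigator, the sponsor and the authorities receive only the DSMC's recommendation until database lock. Section 11.1 mentions collaborators who do statistical analysis, but does not name them or say that they are independent, so someone has to be assigned to this task.

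Otherwise the change is wording in Appendix 5 and, for the alternative, in 9.2.1.

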## **A5.4 Interim Analyses Reporting:**

The P.I will be responsible to present interim findings to the DSMC, the trial sponsor and regulatory health authorities of Foshan Science and Technology Bureau, Guangdong Provincial Health Commission, China.

## **A5.6 Trial Audit:**

Members of the DSMC committee will meet in person, or virtually over Tencent Web Conference , once in every 6 months, to discuss findings from the monthly reports and interim report submitted by the P.I. Decisions taken will be by majority vote of the committee, independent from the sponsor and investigators.
